## Abstract

**Background:**

Cubital tunnel syndrome is the second most common entrapment neuropathy of the upper extremity. Surgical decompression of the ulnar nerve aims to improve complaints and prevent permanent damage to the nerve. Open and endoscopic release of the cubital tunnel are both used in common practice, but none has proven to be superior. This study assesses patient reported outcome and experience measures (PROMs and PREMs respectively), in addition to objective outcomes of both techniques.

**Methods:**

A prospective single-center open randomized non-inferiority trial will take place at the Plastic Surgery Department in the Jeroen Bosch Hospital, the Netherlands. 160 patients with cubital tunnel syndrome will be included. Patients are allocated to endoscopic or open cubital tunnel release by randomization. The surgeon and patients are not blinded for treatment allocation. The follow-up time will take 18 months.

**Discussion:**

Currently, the choice for one of the methods is based on surgeon’s preferences and degree of familiarity with a particular technique. It is assumed that the open technique is easier, faster and cheaper. The endoscopic release, however, has better exposure of the nerve and reduces the chance of damaging the nerve and might decrease scar discomfort. PROMs and PREMs have proven potential to improve the quality of care. Better health care experiences are associated with better clinical outcome in self-reported post-surgical questionnaires. Combining subjective measures with objective outcomes, efficacy, patient treatment experience and safety profile could help differentiating between open and endoscopic cubital tunnel release. This could aid clinicians in evidence based choices towards the best surgical approach in patients with cubital tunnel syndrome.

**Trial registration:**

This study is registered prospectively with the Dutch Trial Registration under NL9556. Universal Trial Number (WHO-UTN) U1111-1267–3059. Registration date 26–06-2021. The URL: https://www.trialregister.nl/trial/9556

## Background

### Background and rationale

Cubital tunnel syndromeis the second most common entrapment neuropathy of the upper extremity [1, 2]. If conservative treatment fails to improve symptoms, surgery is indicated. Forsimple surgical decompression, two methods are being used in common practice: open release and endoscopic release. There is ongoing debate as to what constitutes the superior surgical approach [3–5].

Previous retrospective and prospective studies have compared the two surgical techniques in terms of clinical improvement, complications and patient satisfaction. Only three prospective studies [6–8] were performed of which only two [7, 8] were randomized, the number of participants was relatively small and they were of moderate quality. The American Society for Surgery of the Hand (2018) therefore states that research data on the optimal surgical treatment for cubital tunnel syndrome remains inconclusive [9]. A more large-sample, high-quality randomized controlled trial (RCT) is needed to verify the outcomes [6, 8, 10–13].

Moreover, according to recent overviews, PROMs and PREMs have enormous potential to improve the quality of care by increasing knowledge about people’s perspective on health quality [14, 15]. In current research on cubital tunnel release, however, PROMs and PREMs have not yet been included. Therefore, including these measurements in trials is an important addition to current literature. We intend to perform a more extensive open RCT with the required number of patients to have enough power to evaluate the clinical effect and patient experience with cubital tunnel release using validated objective outcome measures, including PROMs and PREM.

At the end of this study we hope to be able to make an evidence-based recommendation on which method has the best efficacy, patient treatment experience and safety profile. Moreover, this study will focus on the longitudinal validity of the Patient-Rated Ulnar Nerve Evaluation (PRUNE) in Dutch.

### Objectives

We hypothesize that endoscopic cubital tunnel release is more effective in treating cubital tunnel syndrome than open cubital tunnel release in both primary and secondary outcomes.

### Primary objective

To compare the change in PROMS between open and endoscopic cubital tunnel release using the Boston Carpal Tunnel Questionnaire (BCTQ).

### Secondary objectives

- To compare the change in PRUNE between open and endoscopic cubital tunnel release compared to the score of the BCTQ;- To compare the PREM between open and endoscopic cubital tunnel release, and assess its association with PROM;- To compare the post-operative recovery of sensibility;- To compare the return to work/full function;- To compare the complications;- To compare the scar aesthetics;- To compare the correlation between Visual Analog Scale (VAS) score (0-10, 0 being no pain to 10 being the worst pain), Bishop score (a 5 point scale, resulting in a total score of poor 0-2, fair 3-4, good 5-7, excellent 8-9) [16], two-point discrimination and both PROMS (BCTQ and PRUNE).

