#### Secondary outcomes

- The difference in change (Δ, preoperatively and postoperatively) in PRUNE score between both treatment groups at 3, 6, 12 and 18 months follow-up;- The difference in PREM between both treatment groups at 3 months follow-up and its effect on the change (Δ, preoperatively and postoperatively) in PROM;- The difference in post-operative recovery of sensibility between both treatment groups at 3, 6 and 12 months follow-up;- The difference in time until return of full function (RTW) in days between both treatment groups;- The difference amount of complications between both treatment groups during the follow-up period of 18 months;- The difference in scar aesthetics between both treatment groups at 12 months follow-up;- The (difference in) correlation between VAS score (0-10, 0 being no pain to 10 being the worst pain), Bishop score (a 5 point scale, resulting in a total score of poor 0-2, fair 3-4, good 5-7, excellent 8-9) [16], two-point discrimination and both PROMs (BCTQ and PRUNE) at 3, 12 and 18 months follow-up;- The difference in surgical characteristics (duration of procedure, length of incision, amount of peroperative subluxation of the nerve after release) between both treatment groups.

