#### Secondary study parameters

- Difference in change in PRUNE: Linear generalized estimating equation (GEE) analyses will be used to study the longitudinal relationship between treatment group (determinant) on the one hand, and BCTQ score (outcome variable) on the other hand. This will be done for the different domains of the PRUNE.- Difference in PREM vs change in PROM: The PREM score is a continuous outcome and will be analyzed using an independent T-test if distributed normally and a Mann–Whitney U test when not. The change in PROM (BCTQ) score is a continuous outcome and will be analyzed using a paired T- test if distributed normally and a Wilcoxon signed rank test when not. To assess the association between PREM scores and PROM change scores, linear regression analyses will be performed. Multivariable regression models will be used to adjust for potential confounding of various patient and disease characteristics, including age, sex, body mass index, smoking and duration of disease. All domains of the PREM (pre-, intra- and postoperative care and communication) were introduced simultaneously in the same model as independent to determine to what extent the variation in treatment outcome between patients could be explained by the experience with health care, as measured by the PREM. The outcome is measured by the beta-coefficient, showing the change in PROM associated with 1 absolute point increase in PREM subscale.- Sensibility: Sensibility is measured using two-point discrimination, resulting in a categorical outcome. The outcome includes > 2 categories and will be compared using a Chi-Squared test.- RTW, Complications, Scar Aesthetics: Return of full function in days, number of complications and scar aesthetics are continuous outcomes and will be analyzed using an independent T-test.- Correlation between VAS, Bishop, two-point discrimination and both PROMs: The association between VAS score, Bishop score, two-point discrimination and PROMs (both BCTQ and PRUNE) will be determined using the Pearson or Spearman correlation, depending on the data distribution. Analyses will be performed in two dimensions: 1) the correlation between preoperative VAS score, Bishop score, two-point discrimination and both PROMs and 2) the association between change in VAS score, Bishop score, two-point discrimination and both PROMs (12-month score minus preoperative score).

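### The PRUNE-BCTQ comparison in the first secondary objective has no explicit outcome or analysis, the longitudinal-validity aim is covered only indirectly, and the PRUNE model names the BCTQ as its outcome

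*Protocol article*

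**What the plan says.** All references are to the protocol article.

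- **Background and rationale.** The authors state that "this study will focus on the longitudinal validity of the Patient-Rated Ulnar Nerve Evaluation (PRUNE) in Dutch". No comparator and no statistic are attached to this aim.
- **Secondary objectives, first item.** "To compare the change in PRUNE between open and endoscopic cubital tunnel release compared to the score of the BCTQ".
- **Secondary outcomes, first item.** "The difference in change (Δ, preoperatively and postoperatively) in PRUNE score between both treatment groups at 3, 6, 12 and 18 months follow-up". The BCTQ is not mentioned.
- **Secondary study parameters, PRUNE entry.** A linear GEE is planned with treatment group as determinant "and BCTQ score (outcome variable) on the other hand. This will be done for the different domains of the PRUNE".
- **Correlation item.** A separate secondary objective relates VAS, Bishop score, "two-point discrimination and both PROMS (BCTQ and PRUNE"). The outcome sets this for "two-point discrimination and both PROMs (BCTQ and PRUNE) at 3, 12 and 18 months follow-up". The analysis says "The association between VAS score, Bishop score, two-point discrimination and PROMs (both BCTQ and PRUNE) will be determined using the Pearson or Spearman correlation", for preoperative scores and for change from before surgery to 12 months.

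**The concern.** An objective, its outcome and its analysis should name the same quantity. For PRUNE the objective brings in the BCTQ, the outcome drops it, and the analysis entry has it in the wrong role. The background aim of longitudinal validity is not tied to any named estimate.

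This matters because the choices that decide a validity result (which pair of instruments, which scale, which time point, which coefficient) would otherwise be made after the data are seen, in a trial where patients, doctors and researchers all know the allocation. Taken literally, the PRUNE entry also repeats the primary BCTQ model, which leaves the between-arm PRUNE difference without a model of its own.

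**Working it through.** The plan gives no figure to reproduce on this point. The check is a comparison of texts, followed by two short calculations.

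**1. Objective, outcome and analysis side by side**

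| Question | Objective or aim | Outcome | Analysis |
|---|---|---|---|
| PRUNE change, open v endoscopic | yes | yes, 3, 6, 12, 18 months | GEE on treatment group, outcome printed as BCTQ |
| PRUNE against BCTQ | yes (trailing clause of first objective) | none | none explicit |
| Longitudinal validity of PRUNE | yes (background only) | none so named | none so named |
| VAS, Bishop, two-point discrimination with both questionnaires | yes | 3, 12, 18 months | preoperative, and 12-month change |

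**2. What the correlation item covers.** It lists five measures. Read as three clinical measures against two questionnaires, it gives 3 × 2 = 6 pairs, of which three involve PRUNE and none is PRUNE with BCTQ. Read as all pairs among the five, it gives 5 × 4 / 2 = 10, one of which is PRUNE with BCTQ. The wording does not settle which is meant.

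**3. Why the treatment coefficient cannot stand in.** Suppose PRUNE change = k × true change + error, where k expresses how well PRUNE tracks change. The arm coefficient then estimates k × (mean true change in one arm − mean true change in the other). If the arms do equally well, the bracket is 0 and the coefficient is 0 for every k. If they differ, only the product is estimated. Neither case isolates k.

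**4. Precision available from the planned data.**

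- n = 144: Sample size section, the number needed before the dropout allowance; 160 × 0.90 = 144. It is assumed that all 144 have both questionnaires before surgery and at 12 months.
- r = 0.5, 0.6, 0.7: assumed, since the article gives no PRUNE-BCTQ correlation.
- Formula: tanh(atanh(r) ± 1.96/√(n − 3)), with 1.96/√141 = 0.165.

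| Assumed r | atanh(r) | Limits on z scale | 95% CI for r |
|---|---|---|---|
| 0.5 | 0.549 | 0.384 to 0.714 | 0.37 to 0.61 |
| 0.6 | 0.693 | 0.528 to 0.858 | 0.48 to 0.70 |
| 0.7 | 0.867 | 0.702 to 1.032 | 0.61 to 0.77 |

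These intervals do not measure the defect. They show that the missing estimate would be usefully precise without further patients or assessments: both questionnaires are already planned outcomes at 12 months.

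**The case against.** The strongest reply is that PRUNE validity is in fact addressed. Correlating change in PRUNE with change in VAS, Bishop score and two-point discrimination is a usual way to examine longitudinal construct validity, and the background does not say that the BCTQ must be the comparator. This stands. A reader might infer that PRUNE is analysed only as an arm difference and that validity is never estimated; the correlation item contradicts both.

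A reader might also take validity to be a twice-stated aim. The word appears only in the background. The clause in the first objective is loose, and could mean no more than setting the PRUNE arm comparison beside the BCTQ one. Even on that reading, the PRUNE arm comparison needs a model with PRUNE as outcome, and the printed entry does not give one.

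Nor does any part of the article propose to read a null arm difference as poor responsiveness, so a forecast of that misreading has no basis in the text.

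Finally, a journal article may leave analysis detail to a fuller protocol or SAP. That covers choices such as standardised response means or how their intervals are formed. It does not cover stated texts that disagree with one another, or a wrongly named outcome variable.

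**Conclusion.** The point holds in a limited form:

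- The PRUNE-BCTQ comparison in the first secondary objective has no explicitly matching outcome or analysis.
- The longitudinal-validity aim is covered only indirectly, by three unlabelled change correlations at 12 months; the treatment-group GEE cannot address it.
- The PRUNE GEE names the BCTQ as its outcome. The next sentence, "This will be done for the different domains of the PRUNE", suggests a drafting slip and shows the intention, but the text should be corrected.
- The correlation time points disagree: 3, 12 and 18 months as outcomes, preoperative and 12-month change in the analysis.

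The matter is secondary and leaves the primary endpoint untouched. It should still be put right, because the repair is cheap and lets the trial answer a question it sets itself. The conclusion rests on the wording and on no numerical assumption; only the intervals depend on the assumed correlations and on 144 complete pairs.

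**What to change.** 1. **Secondary study parameters, PRUNE entry:** name the PRUNE score as the outcome variable of the GEE.
2. **Secondary outcomes and Secondary study parameters:** add the correlation of PRUNE change with BCTQ change from before surgery to 12 months, separately for the BCTQ symptom and function scales, arms pooled, with a 95% CI. The Pearson-or-Spearman rule already planned can be kept. State which PRUNE score is used.
3. **Label** this correlation, together with the existing change correlations of VAS, Bishop score and two-point discrimination with PRUNE, as the longitudinal-validity analysis.
4. **Align the time points** of the correlation item between outcome and analysis. The Follow-up section describes the 18-month contact as questionnaires completed at home, so check that two-point discrimination and the Bishop score are available then before keeping 18 months for them (the visit table is not shown in the text reviewed).

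Standardised response means for the two instruments are optional. If the sponsor does not want the PRUNE-BCTQ comparison, the alternative is to delete the clause from the objective and tie the background aim to the existing change correlations.

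Cost: a few lines of wording and minor analysis work, with no new data.

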### Trial design

This is a prospective randomized non-inferiority trial with two parallel study groups to assess the efficacy, patient treatment experience and safety profile of the open or endoscopic release in patients with cubital tunnel syndrome.

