### Outcomes

#### Primary outcome

The difference in change (Δ, preoperatively and postoperatively) in BCTQ score between both treatment groups at 3, 6 and 12 and 18 months follow-up.

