### Sample size, recruitment and consent

Malay et al. identified a minimal clinically import change (MCIC) at 3, 6, and 12 months’ time-points of 0.4, 0.7, and 0.7 points on a 5-point scale for symptom severity score of the BCTQ questionnaire and 0.3, 0.3, and 0.4 points on a 5-point scale for function status scale [19]. The standard deviation used is 0.7, based on a 12 months follow-up after decompression [20].

Using a sample size formula for continuous outcomes in a longitudinal study, a total of 144 patients will be needed (α = 0.05, β = 0.80). Taking into account a dropout of 10%, we will include 160 patients.

Patients will be identified and invited for the study at the neurological outpatient clinic. Study information will be given and time to overthink participation. During the first outpatient clinic visit at the plastic surgery department, patients will get the chance to ask questions and sign written informed consent with the surgeon or resident present.

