#### Analysis plan

Descriptive statistics will be provided using mean with standard deviation (SD), median with interquartile range (IQR) or frequencies/percentages depending on the type of distribution of the data. Distribution of data will be assessed using histograms and skewing.

Values of *p* < 0.05 will considered statistically significant. All analysis will be on an intention- to-treat basis. We will correct for multiple testing, *P*-values will be corrected by the Bonferroni method [21].

For exclusion and dropout, numbers and reasons are reported to ensure internal validity. A flow- chart will show the number of patients lost during follow-up including reasons for the loss of follow-up. An analysis on basic characteristics will be performed to control for selection bias. Missing values will be imputed using multiple imputations when meeting the assumption of missing completely at random/missing at random (MCAR/MAR), as imputation will always increase precision and often also reduce bias [22, 23].

Table 1 shows the variables at each study visit.

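### The trial is labelled non-inferiority, but its hypothesis is superiority, no margin or direction is named, and the stated p-value rule cannot support a non-inferiority conclusion

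*Protocol article*

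**What the plan says.** All references are to the protocol article.

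- **Label.** The Trial design section reads "This is a prospective randomized non-inferiority trial with two parallel study groups". The Methods paragraph of the Abstract agrees: "A prospective single-center open randomized non-inferiority trial will take place".
- **Hypothesis.** The Objectives section reads "We hypothesize that endoscopic cubital tunnel release is more effective in treating cubital tunnel syndrome than open cubital tunnel release", and applies this to primary and secondary outcomes alike.
- **Primary outcome.** The difference in change "in BCTQ score between both treatment groups at 3, 6 and 12 and 18 months follow-up".
- **Sample size.** The section cites a study that "identified a minimal clinically import change (MCIC) at 3, 6, and 12 months". The values are "0.4, 0.7, and 0.7 points on a 5-point scale for symptom severity score" and "0.3, 0.3, and 0.4 points on a 5-point scale for function status scale". It adds an SD of 0.7, an alpha of 0.05, a β of 0.80 (evidently meaning power), 144 patients, and 160 after 10% dropout. It does not say which value was the target, whether the test is one- or two-sided, or whether any value is a non-inferiority margin.
- **Analysis.** The primary analysis is a linear GEE for each BCTQ domain, giving one treatment coefficient. The Analysis plan sets significance at p below 0.05 with Bonferroni correction, and says "All analysis will be on an intention- to-treat basis".

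**The concern.** Non-inferiority and superiority are different confirmatory questions. A non-inferiority claim needs three things fixed in advance: which technique is to be shown no worse than which, by how much it may be worse, and which confidence limit must stay inside that margin. The article gives none of these. The one rule it does give separates significant from non-significant results.

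This matters most if the p-value is above 0.05. Under a non-inferiority label, a reader could take that result as showing that the techniques are equally good. A non-significant difference does not show this, because it is also a common result when one technique is worse by an amount that matters. Bonferroni correction aggravates the problem. It protects against false claims of a difference, but it makes non-significance more likely, and so makes this misreading easier.

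**Working it through.** **1. The sections side by side.** The Abstract and Trial design sections say non-inferiority. The Objectives say more effective. The sample size section names no margin, direction or sidedness. The analysis sections compare a p-value with 0.05 and compare no confidence limit with anything. Nothing links the label to the hypothesis, for example by testing non-inferiority first and superiority second.

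**2. Does the figure of 144 settle which framework was used?** From the article: SD 0.7, alpha 0.05, power 0.80, 1:1 allocation. Assumed: target difference 0.3 (the smallest MCIC) and a two-sided test.

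Single time point: n per arm = 2 × (0.7 × (1.960 + 0.842) / 0.3)² = 85.5, so 86 per arm and 172 in total, not 144.

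Longitudinal formula with T visits and within-patient correlation ρ: multiply 85.5 by [1 + (T − 1)ρ] / T. With T = 4, the number of follow-up times in the primary outcome, 72 per arm requires ρ of about 0.79: 85.5 × (1 + 3 × 0.79) / 4 = 72.0. So 144 is compatible with a target of 0.3, but the article does not give the T or ρ needed to confirm it. Dropout is handled correctly: 144 / 0.9 = 160.

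With a true difference of zero, a one-sided 0.025 non-inferiority calculation with margin 0.3 gives the same number. The arithmetic therefore cannot tell the two frameworks apart.

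**3. How often would a truly worse technique give p above 0.05?** Inputs: 72 per arm, SD 0.7, T = 4, uncorrected two-sided alpha of 0.05. The correlation is not stated, so a range is used.

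SE = 0.7 × √[(2/72) × (1 + 3ρ)/4]

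P(p > 0.05) = Φ(1.96 − d/SE) − Φ(−1.96 − d/SE), where d is the true deficit.

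| Assumption | SE | d = 0.2 | d = 0.3 |
|---|---|---|---|
| ρ = 0.5 | 0.092 | 42% | 10% |
| ρ = 0.79 | 0.107 | 54% | 20% |
| ρ = 0.9 | 0.112 | 57% | 24% |
| Single time point | 0.117 | 60% | 27% |

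The 20% in the ρ = 0.79 row is not an independent result. That correlation was chosen to give 80% power at 0.3, so 20% is simply one minus the power. For comparison, a non-inferiority test with margin 0.3 at one-sided 0.025 would wrongly declare non-inferiority 2.5% of the time at a true deficit of 0.3.

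**4. Effect of Bonferroni.** The article does not define the family of tests. If only two tests were counted (critical value 2.241), the figure at ρ = 0.79 and d = 0.3 would rise from 20% to 29%. A larger family would raise it further.

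**5. Sample size if non-inferiority were kept.** Accept the longitudinal gain implied by 144 at 0.3, one-sided alpha 0.025, 80% power, true difference zero and no multiplicity correction. A margin m then needs 144 × (0.3/m)². At m = 0.3 this is 144 (160 with dropout). At m = 0.2 it is 144 × 2.25 = 324 (324 / 0.9 = 360).

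**The case against.** Three replies carry weight.

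First, this is a condensed article. A per-protocol analysis and the details of confidence-limit reporting are often left to the full protocol or the analysis plan. That is fair, and their absence is not counted here as a separate error. The framework is another matter. The label and the hypothesis are both stated and they disagree, and an unseen document does not remove that conflict.

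Second, expecting a benefit is compatible with testing non-inferiority first and superiority next. That is true in principle, but the article describes no such sequence, and it would still need a margin.

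Third, the size of the problem depends on inputs that the article does not state: the target difference, the number of visits, the correlation and the number of tests. This stands, which is why the figures are given as a range and as an illustration.

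Two stronger readings are tempting and are not supported. A reader might infer that the sample size was calculated for superiority; step 2 shows that 144 fits either framework at 0.3. A reader might also infer that the investigators intend to read non-significance as non-inferiority. No section says so, and the text supports only that the result could be read that way.

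**Conclusion.** The point holds. The labelled design and the stated hypothesis conflict, no margin or direction is given, and the stated decision rule cannot deliver a non-inferiority conclusion. These findings rest on the text alone and on no assumption.

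The consequence is conditional. If non-significance were taken as non-inferiority, a technique truly worse by 0.3 points would pass in about 10% to 24% of trials (27% at a single time point), and one worse by 0.2 in about 42% to 57% (60%). This assumes 72 per arm, SD 0.7, four visits, correlation 0.5 to 0.9 and uncorrected alpha. Any Bonferroni correction increases the figures.

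The matter must be resolved before data are seen, because the trial's main conclusion depends on which framework applies and a later choice would be post hoc.

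**What to change.** **Preferred.** Remove the non-inferiority label from the Abstract and the Trial design section, and describe a two-sided superiority trial, consistent with the Objectives. State that p above 0.05 will not be read as equivalence or non-inferiority. Report the 95% confidence interval of the GEE treatment coefficient against the MCIC of each BCTQ domain. Say which MCIC value applies, because the coefficient averages over time and no value is listed for 18 months. This is a wording change and needs no extra patients.

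**If the sponsor keeps non-inferiority.** Before data are seen, fix:
- a justified margin for each BCTQ domain (the listed MCICs differ between domains and are not presented as between-group margins);
- which technique is to be shown non-inferior to which;
- the one-sided alpha and the confidence-limit rule;
- a supporting per-protocol analysis beside intention to treat.

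Then recheck the sample size. The 144 patients before dropout suffice only for a margin of about 0.3, with the assumed correlation and no multiplicity correction. On the same assumptions, a margin of 0.2 would need about 324 (360 with dropout). This route may therefore cost many more patients.
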